### Measurements

Baseline characteristics, including smoking habit, NYHA functional classification, etiology of CHF, hypertension, dyslipidemia, and other complications will be screened prior to randomization. The medication status of the study agents, and the participant’s background treatment, BW, BP, and heart rate will be also measured at each visit. A chest X-ray is taken at baseline and at the final visit. An echocardiogram is performed at screening, baseline, and the final visit to measure LVEF using the modified Simpson method and E/e’. The echocardiograms will be evaluated by technicians at each local site. Blood and urine tests will be checked at each visit (details listed in Additional file 3). Specific biomarkers, including NT-proBNP, high-sensitivity C reactive protein (hsCRP), serum cystatin C, pentraxin 3 (PTX3) (SRL, Inc. Tokyo, Japan), high-sensitivity troponin I (Abbot Japan, Tokyo, Japan), receptor for advanced glycation end products (RAGE), angiopoietin-like protein 2 (ANGPTL2), interleukin 8 (IL-8), and periostin (Saga University) will be measured at a central laboratory at baseline and the final visit. CHF-related quality of life is evaluated by scaled responses to the Minnesota Living with Heart Failure (MLHF) questionnaire at baseline and the final visit. The occurrence of CV events, including all-cause death, non-fatal myocardial infarction, non-fatal stroke, hospitalization for heart failure, and additional medications or dosage increases of drugs due to aggravation of heart failure will be evaluated.

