**Methods:**

A total of 250 patients with type 2 diabetes who are drug-naïve or taking any anti-diabetic agents and suffering from chronic heart failure with a New York Heart Association classification I to III will be randomized centrally into either canagliflozin or glimepiride groups (1: 1) using the dynamic allocation method stratified by age (<65, ≥65 year), HbA1c level (<6.5, ≥6.5 %), and left ventricular ejection fraction (<40, ≥40 %). After randomization, all the participants will be given the add-on study drug for 24 weeks in addition to their background therapy. The primary endpoint is the percentage change from baseline in NT-proBNP after 24 weeks of treatment. The key secondary endpoints after 24 weeks of treatment are the change from baseline in glycemic control, blood pressure, body weight, lipid profile, quality of life score related to heart failure, and cardiac and renal function.

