### Trial endpoints

NT-proBNP is used widely to monitor the therapeutic efficacy of agents for heart failure in clinical trials and is established as a prognostic biomarker for heart failure [21–23]. In addition, NT-proBNP-guided treatment for heart failure has been demonstrated to improve clinical outcomes in a randomized trial [24]. Therefore, the percent change in NT-proBNP levels from baseline to 24 weeks will be used as the primary endpoint in the CANDLE trial. The secondary endpoints are the values and changes in parameters after 24 weeks of treatment (or at discontinuation), including: (1) NT-proBNP, (2) glycemic control (HbA1c, fasting plasma glucose, plasma insulin, HOMA-R and HOMA-beta), (3) clinic systolic and diastolic BP and home BP (optional), (4) BW, (5) biochemical tests (lipid profiles and uric acid), (6) quality of life (MLHF scores) (7) echocardiographic cardiac function parameters (LVEF and E/e’) and severity and change in NYHA functional classification, and (8) renal function parameters (serum creatinine level, estimated glomerular filtration rate (eGFR), urinary albumin excretion, and urine L-FABP). Other secondary endpoints include clinical outcomes such as CV events, including all-cause death, non-fatal myocardial infarction, non-fatal stroke, hospitalization for heart failure, and changes in medications related to aggravation of heart failure. Safety endpoints include adverse effects and adverse drug reactions observed during treatment with the study drugs. The exploratory endpoints are changes in specific biomarkers after 24 weeks of treatment, including high-sensitivity troponin I, hsCRP, serum cystatin C, PTX3, RAGE, ANGPTL2, IL-8, and periostin. The findings of these biomarker assays may, in part, provide mechanistic insights on the effect of canagliflozin on CV pathogenesis.

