#### Analysis plan

The analyses of the primary and secondary endpoints will be performed in the FAS, which includes all patients who received at least one dose of treatment during the study period and did not have any serious violation of the study protocol, and had data collected after commencement of treatment. For the baseline characteristics, the summary statistics will comprise frequencies and proportions for categorical variables, and means and standard deviations for continuous variables. The patient characteristics will be compared using Chi square tests for categorical variables, and t tests for normally distributed continuous variables or Wilcoxon rank sum tests for continuous variables with a skewed distribution.

For the primary analysis comparing treatment effects, the least square mean and its 95 % confidence interval will be estimated using analysis of covariance (ANCOVA). To test for non-inferiority of the primary endpoint, the ANCOVA will be applied adjusted for age (<65, ≥65 year), HbA1c level (<6.5, ≥6.5 %), and left ventricular ejection fraction (LVEF; <40, ≥40 %). The secondary analysis will be performed in the same manner as the primary analysis.

All comparisons are planned and all *p* values will be two sided. *P* values <0.05 will be considered statistically significant. All statistical analyses will be performed using SAS software version 9.4 (SAS Institute, Cary, NC, USA). The statistical analysis plan will be developed by the principal investigator and a biostatistician before completion of patient recruitment and database lock.

Trial organization and oversight (details in Additional file 4).

Principal investigators of the CANDLE trial are [name] (Chief), Department of Cardiovascular Medicine, Saga University and [name], Department of Cardiology, Nagoya University Graduate School of Medicine. The Steering Committee will carry out planning, operating, analyzing, and presentation of the trial. The Executive Committee will supervise the trial design and operation of the study. The roles of DSMB and CEC are described in the section of Endpoint adjudication. The trial secretariat is in DOT INTERNATIONAL CO., LTD, Tokyo, Japan. Each of data management, monitoring, statistical analyses, and audit will be independently implemented on the basis of outsourcing agreement.

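### The stated ANCOVA for LVEF and E/e' uses no continuous pre-treatment echo reading, although two are taken; entering both as covariates is an optional gain in precision

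*Protocol article*

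**What the plan says.** - **Schedule (protocol article, Measurements):** "An echocardiogram is performed at screening, baseline, and the final visit to measure LVEF using the modified Simpson method", and E/e' on the same scans. There are two pre-treatment scans and one final scan. The same section adds: "The echocardiograms will be evaluated by technicians at each local site".
- **Endpoint (Abstract, Methods):** the key secondary endpoints are changes "from baseline in glycemic control, blood pressure, body weight, lipid profile, quality of life score related to heart failure, and cardiac and renal function". The Trial endpoints section lists "echocardiographic cardiac function parameters" (LVEF and E/e') among the secondary endpoints. It refers both to values and to changes after 24 weeks, and does not say which pre-treatment scan is the reference.
- **Model (Analysis plan):** the ANCOVA is adjusted for age (below or from 65 years), HbA1c (below or from 6.5%) and LVEF (below or from 40%). Then: "The secondary analysis will be performed in the same manner as the primary analysis". No continuous pre-treatment value of the outcome is listed.
- **Stated use of the screening scan (Randomization and treatment):** screening LVEF, split at 40%, is a minimization factor. The same LVEF categories appear in the ANCOVA. No use is stated for screening E/e'.

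**The concern.** The trial asks whether canagliflozin worsens heart failure compared with glimepiride. LVEF and E/e' are its echocardiographic measures of that. They are read at each site, so reading error is a practical concern. A patient's own earlier readings are usually the best available predictors of the week-24 reading. A model that carries only an LVEF category leaves most of that information out, and for E/e' it leaves out the outcome's own history altogether. The treatment comparison stays valid, but its confidence interval is wider than the collected data require, so a real difference in cardiac function is easier to miss.

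**Working it through.** **Inputs.** From the protocol article: two pre-treatment readings, one final reading, and three two-category covariates. The article gives no SD, correlation, sample size or power for LVEF or E/e', so there is no figure of the plan's own to reproduce. The 125 per group in Sample size estimation concerns NT-proBNP only. All correlations below are assumptions.

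**Notation.** S is the screening reading, B baseline and Y week 24, each with variance 1. Write r12 = corr(S,B), r23 = corr(B,Y) and r13 = corr(S,Y). Where all three are equal, call the common value r.

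**Step 1: the stated model, taking change from baseline as the outcome.** Var(Y − B) = 2(1 − r23), which is 0.60 at 0.7. The LVEF category comes from S, and cov(Y − B, S) = r13 − r12, which is zero when correlations are equal. The category then recovers nothing. A simulation of one million draws, with 20%, 30% or 40% of patients below the cut, agrees: 0.60 with or without it at r = 0.7.

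**Step 2: add the continuous baseline reading.** Residual variance is 1 − r23². At 0.7 this is 1 − 0.49 = 0.51, which is 15% below 0.60. The result is the same whether the outcome is the week-24 value or the change.

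**Step 3: add the continuous screening reading as well.** Residual variance is 1 − (r23² + r13² − 2·r12·r23·r13)/(1 − r12²). With r13 = r23 = r this reduces to 1 − 2r²/(1 + r12).

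| r12 | r23 | r13 | Baseline only | Both readings | Reduction |
|---|---|---|---|---|---|
| 0.8 | 0.7 | 0.6 | 0.510 | 0.506 | under 1% |
| 0.9 | 0.7 | 0.7 | 0.510 | 0.484 | 5% |
| 0.8 | 0.6 | 0.6 | 0.640 | 0.600 | 6% |
| 0.8 | 0.7 | 0.7 | 0.510 | 0.456 | 11% |
| 0.7 | 0.7 | 0.7 | 0.510 | 0.424 | 17% |
| 0.8 | 0.8 | 0.8 | 0.360 | 0.289 | 20% |

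First row in full: (0.49 + 0.36 − 2 × 0.8 × 0.7 × 0.6)/(1 − 0.64) = 0.178/0.36 = 0.494, and 1 − 0.494 = 0.506.

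**Step 4: both readings against the stated model.** At all correlations 0.7: 0.60 to 0.424, or 29% lower. At all 0.8: 0.40 to 0.289, or 28% lower. In the first row of the table, 0.60 to 0.506 is 16% before any credit for the LVEF category, and nearly all of it comes from the baseline covariate.

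**Step 5: LVEF with its category kept.** For LVEF the screening category already carries part of the screening information once continuous baseline is in the model. In the simulation, baseline plus category gives 0.47 to 0.48 at r = 0.7 and 0.33 to 0.34 at r = 0.8. Adding the continuous screening value then saves 10 to 12% and 13 to 15%. For E/e' the category is not derived from the measure itself, so the table is the better guide.

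**Step 6: price of the extra covariate.** It costs one degree of freedom. With 250 patients, or 225 after the assumed 10% dropout, about 244 or 219 remain (subtracting intercept, treatment, three factors and one reading). The price is roughly 1/244 to 1/219, or 0.4 to 0.5% of variance.

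**Step 7: averaging the two readings instead.** Var(Y − (S + B)/2) = 1 + (1 + r12)/2 − (r13 + r23). With all correlations equal this is 1.5(1 − r), 25% below 2(1 − r). With r12 = 0.8, r23 = 0.7 and r13 = 0.6 it is 1 + 0.9 − 1.3 = 0.60, the same as from baseline alone. Averaging helps only while r23 − r13 is below (1 − r12)/2.

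**The case against.** The strongest reply is that the handling of repeated pre-treatment values belongs in the statistical analysis plan, which is not shown and which the article says is still to be written. Change from the baseline visit is also an ordinary, valid endpoint, and nothing in the article is contradictory here. Most of this stands. It does not cover the covariate list, which the article states and extends to the secondary endpoints.

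A reader might infer more than the documents support:

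- **That change is taken from the baseline scan alone and the screening scan is discarded.** The Abstract speaks of change from baseline, but no section defines the echo reference value or rules out using both scans. Screening LVEF also has a stated job in the minimization, and the same categories enter the ANCOVA.
- **That averaging the two scans would cut variance by 25% at any correlation, worth a third more patients.** That needs the screening scan to predict week 24 as well as the baseline scan does. If the earlier scan predicts less well, the gain can vanish (step 7).
- **That averaging is free of selection effects because entry has no LVEF cut-off.** Table 1 sets none, but Trial population and recruitment says that echocardiography contributes to the classification of heart failure, so the screening scan may inform eligibility.

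The 4-week washout for users of another SGLT2 inhibitor is a further reason not to treat the two scans as interchangeable.

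**Conclusion.** The point holds as a missed efficiency on two secondary measures. The stated model carries no continuous pre-treatment reading of LVEF or E/e'. Entering both would lower residual variance by about 28 to 29% against that model if all correlations are 0.7 to 0.8. The part due to the screening reading alone, over one continuous baseline covariate, ranges from under 1% to about 20%, and somewhat less at the top for LVEF if its category stays in the model.

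These figures rest on assumed correlations, equal variances and a linear relation; the documents supply none of them. No bias or invalid inference is involved. The primary endpoint is untouched, since NT-proBNP is measured only at baseline and the final visit. This is an optional improvement, not an error.

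**What to change.** In the analysis plan, for LVEF and E/e' only: analyse the week-24 value (or the change) by ANCOVA with the continuous baseline reading and the continuous screening reading both as covariates, alongside the three minimization factors. Keep the baseline visit as baseline; do not replace it with the mean of the two scans. For patients washed out of an SGLT2 inhibitor between the scans, the screening scan may reflect a different state, so repeat the analysis with the baseline reading alone as a check.

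The cost is a sentence or two in the analysis plan and one extra model run for each measure. No further scan, visit or reader is needed, and the loss of one degree of freedom is negligible at this sample size.

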### Safety

Based on the intention-to-treat entire population, safety will be checked by recording the following adverse effects throughout the duration of the study: hypoglycemia, genital infections, urinary tract infections, excess osmotic diuresis signs (increased urinary frequency, mouth dryness, or polyuria), and hypovolemic symptoms. A previous study has reported an increased prevalence of hypoglycemia with sulfonylureas than with canagliflozin [14]. We therefore need to pay careful attention to the development of hypoglycemia, especially in patients assigned to the glimepiride group, despite this drug being initiated at a low dose in the study. If the investigators confirm these adverse effects, the grade of severity, treatment, outcomes, and relationship to the study drug will be assessed. The criteria for withdrawal from the trial are listed in Table 3. In addition, the incident of withdrawal from the study will be reported promptly to the Data and Safety Monitoring Board (DSMB) by the trial organizer.

**Table 3 Tab3:** Discontinuance criteria

Severe hypoglycemia that needs some support by family members or medical care at medical settings
Seriously poor glycemic control such as ≥HbA1c 10.0 %
Diabetic ketoacidosis
Dehydration
Considered inappropriate to continue the study by investigators due to aggravation of primary disease or complications
Considered inappropriate to continue the study by investigators due to adverse side effects of the study drug
Offer for participation declined by participants
Considered inappropriate to continue the study by investigators due to some other reason

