### Trial population and recruitment

We aim to recruit a total of 250 participants across approximately 35 sites in Japan. Recruitment for this trial began in October 2015 and will be completed by December 2017. Eligible patients in the trial are T2DM patients with CHF (aged ≥20 years) who comply with all the enrollment criteria. The detailed inclusion and exclusion criteria are listed in Table 1. Briefly these criteria include: (1) Patients with appropriately diagnosed T2DM, who are drug-naïve or taking any anti-diabetic agent; (2) T2DM clinically requiring a start or change of an anti-diabetic agent; (3) complicating NYHA functional classification I to III CHF, but not IV, with maintenance of the clinical condition and unchanged medical treatment for CHF, including angiotensin-converting enzyme inhibitors, angiotensin II receptor blockers, beta-blockers, and diuretic agents for 4 weeks prior to screening. In the trial, CHF is classified comprehensively by skilled cardiologists using several findings, including clinical symptoms (the Framingham criteria for congestive heart failure and NYHA functional classification), history of hospitalization for heart failure, and clinical tests such as echocardiography and biomarkers. However, there is no limitation on the NT-proBNP level at enrollment. Prior to eligibility screening, every participant is required to receive an adequate explanation based of the trial plan, with written informed consent then being obtained from each patient.

**Table 1 Tab1:** Detailed inclusion and exclusion criteria

Inclusion	Exclusion
Adults (aged ≥20 years)	Type 1 diabetes mellitus
T2DM patients who need to start or who are possibly changing or adding an anti-diabetic agent	History of diabetic ketoacidosis, diabetic coma, or hypoglycemic attack ≤6 months prior to informed consent
CHF (NYHA functional classification I to III)	Severe renal dysfunction (eGFR <45 ml/min/1.73 m^2^) or patients receiving dialysis
Without change in NYHA functional classification or drugs for heart failure 4 weeks prior to eligibility	Severe liver dysfunction (at least threefold higher AST or ALT more than the upper limit of the facilities reference value
The patient provided written informed consent to participate in the study	CHF (NYHA functional classification IV)
	Patients with pituitary or adrenal dysfunction
	Patients with malnutrition, starvation, irregular eating pattern, lack of dietary intake, or debilitation

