	Patients with excess alcohol intake
	Patients in perioperative period around trial screening
	Patients with severe infection or trauma at trial screening
	Patients with a gastrointestinal disorder, such as diarrhea or vomiting
	Patients with low body weight (BMI **<**18.5 kg/m^2^)
	History of coronary artery disease, coronary vascularization, open-heart surgery, stroke, or transient ischemic attack ≤3 months prior to eligibility
	Patients with a malignancy
	History of hypersensitivity to ingredients of SGLT2 inhibitors or sulfonylureas
	Pregnant or suspected pregnancy in females
	Lactating female
	Considered inappropriate for the study by investigators due to other reasons

*ALT* alanine aminotransferase, *AST* aspartate transaminase, *BMI* body mass index, *CHF* chronic heart failure, *eGFR* estimated glomerular filtration rate, *NYHA* New York Heart Association, *SGLT2* sodium glucose cotransporter 2, *T2DM* type 2 diabetes mellitus

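### Table 3 makes seriously poor glycemic control a reason to leave the trial, not only to stop study drug, so such a patient can be in the FAS without a 24-week NT-proBNP

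*Protocol article*

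**What the plan says.** All references are to the protocol article; the full protocol and the SAP are not at hand.

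- **Safety.** The text states that "The criteria for withdrawal from the trial are listed in Table 3". It then says that withdrawals from the study are reported to the DSMB. Table 3 itself is titled as discontinuance criteria. One row is "Seriously poor glycemic control such as ≥HbA1c 10.0" %, and three further rows turn on the investigator judging it inappropriate for the patient to continue the study.
- **Measurements.** NT-proBNP is one of the biomarkers that "will be measured at a central laboratory at baseline and the final visit".
- **Trial endpoints.** For the primary endpoint, "the percent change in NT-proBNP levels from baseline to 24 weeks will be used as the primary endpoint". The secondary endpoints, with NT-proBNP first in the list, are taken after 24 weeks or at discontinuation. That alternative is not attached to the primary endpoint.
- **Analysis plan.** The FAS keeps every patient who took at least one dose, had no serious protocol violation and has data from after the start of treatment.
- **Randomization and treatment.** Treatment is open-label; the assessors are blinded.

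**The concern.** Stopping a drug and leaving a trial are different events. Seriously poor glycemic control is a reason to change a patient's diabetes treatment. It is not in itself a reason to stop observing the patient, yet the text attaches trial exit to it.

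The primary endpoint is tied to one time point. If a patient leaves before week 24, the value that defines the endpoint is not observed, although the patient may still count in the primary analysis set. An SAP can say how to handle a missing value, but it cannot recover a sample that was never drawn, so this has to be settled in the protocol.

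The row gives HbA1c of 10.0 % only as an example, so the decision is a judgement, and it is made by an investigator who knows whether the patient takes canagliflozin or glimepiride. Missing primary data created in that way invite questions that continued follow-up would avoid. Follow-up would also keep the clinical events listed among the secondary endpoints, such as death and hospitalization for heart failure, under observation.

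**Working it through.** The point rests mainly on the text, so the first step is to follow one patient through the stated rules.

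| Step | Rule (section) | Result |
|---|---|---|
| 1. Randomized, takes study drug, seen at week 4 or 12 | Visits at 4, 12 and 24 weeks (Trial outline and follow-up); blood tests at each visit (Measurements) | Has data after the start of treatment |
| 2. Judged to have seriously poor control before week 24 | Table 3 (Safety) | Withdrawn from the trial |
| 3. Analysis set | FAS definition (Analysis plan) | Stays in, absent a serious violation |
| 4. NT-proBNP at discontinuation | Secondary endpoints (Trial endpoints) | May be available |
| 5. NT-proBNP at 24 weeks | Primary endpoint (Trial endpoints) | Not available after exit |

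Steps 3 and 5 together give the conclusion: in the FAS, without the 24-week value. Step 4 limits it: the second measurement may be brought forward rather than lost. If the final visit in Measurements means the last visit attended, the result is the same, because that sample is still not a 24-week one.

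**The plan's own figure.** Sample size estimation gives 125 per group with SD 0.80 (log scale), margin 1.1, one-sided 2.5 %, power of at least 80 %, a true difference of 18 % and 10 % dropout. I read the 18 % as a ratio of 0.82, which is an assumption.

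- n per arm = 2 × SD² × (1.960 + 0.842)² / d².
- With d = log(1.1) − log(0.82) = 0.2938: n = 117, and 117 / 0.9 = 130.
- With the margin taken as 0.10 on the log scale, d = 0.10 − log(0.82) = 0.2985: n = 113, and 113 / 0.9 = 126, which is close to the stated 125.

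The present point does not depend on which reading was used. What matters is that dropout is already allowed for: 0.10 × 250 = 25 patients.

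**Scale of one affected patient.** 1/250 = 0.4 % of the trial, 1/125 = 0.8 % of an arm, and 1/25 = 4 % of the dropout allowance. These are shares per patient, not estimates of an effect. The article gives no HbA1c distribution and no expected rate of this event, so they cannot be multiplied up.

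**The case against.** **The article does not say that nothing is measured after withdrawal.** True. The title of Table 3 alone could mean stopping the drug, and the full protocol may provide for later visits. But the introducing sentence and three of the rows speak of the trial or the study. The point is that stated rule, not a detail the article left out.

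**A reader might infer that one of the two planned NT-proBNP measurements is lost.** The documents do not support that, because a value at discontinuation is foreseen among the secondary endpoints. Only the 24-week timing of the primary value is lost.

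**A reader might infer that the entry criteria contradict the stop rule.** Table 1 admits "T2DM patients who need to start or who are possibly changing or adding an anti-diabetic agent" and sets numeric limits elsewhere, for example "Severe renal dysfunction (eGFR <45 ml/min/1.73 m^2^) or patients receiving dialysis", but sets no HbA1c ceiling. This is not a contradiction. The 10.0 % is an example, a high value before treatment differs from poor control on treatment, and investigators may exclude a patient "Considered inappropriate for the study by investigators due to other reasons". Randomization and treatment also allows rescue with other anti-diabetic agents. An entry ceiling would be a debatable trade-off and is not proposed.

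**A reader might infer that the safety analysis is undermined.** The Safety section says that "safety will be checked by recording the following adverse effects throughout the duration of the study", on the intention-to-treat population. But Trial endpoints defines the safety endpoints as effects seen during treatment with study drug, so exit after stopping the drug does not clearly conflict with it.

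**Values after a switch of treatment can pull the arms together.** This stands, and it is not neutral for non-inferiority: dilution could hide a true harm or weaken the evidence of a true benefit. It bears on how such values are analysed, not on whether to collect them.

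**Conclusion.** The point holds as a minor, inexpensive improvement. As written, a patient withdrawn under the glycemic row before week 24 can be in the FAS with an NT-proBNP value at discontinuation at best and no 24-week primary value. The same follows from the other Table 3 rows, so this row is an instance of a general rule and not a special defect.

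The conclusion assumes that withdrawal from the trial means what it says and that the full protocol does not override it. The number of patients is unknown and probably small, since rescue therapy is available. Withdrawals that fall within the 25 dropouts allowed for do not change the planned power. A reader might go on to infer a biased comparison or an underpowered trial. The documents give no rate of this event and no difference in rate between arms, so neither can be computed and neither is claimed.

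**What to change.** Keep the HbA1c threshold. Define this row, and the other Table 3 rows except the participant's own refusal, as stopping study drug. State that diabetes treatment may then change as clinically needed, that the patient stays in follow-up, and that the already scheduled week-24 NT-proBNP is drawn and flagged as off study drug. Report the non-inferiority comparison both with and without the flagged values, so that any pull of the arms towards each other can be seen.

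The cost is a short protocol change, one already planned visit and sample per affected patient, and one added analysis. No new procedure is needed.
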